## 2.9 Rules for Early Stopping

The patient had the right to withdraw consent and stop or postpone the assessment interviews or adherence questionnaires if he/she became upset at any time during the study period. The participant may choose to stop participating in the study at any time without any penalty or limitation in the usual clinical services provided. Any adverse event and/or unanticipated problem involving any risk to the participants will be reported to the SEHA REC. Moreover, any problems that may arise, such as significantly abnormal laboratory results, medication side effects or complications in blood sample collection, will be treated instantly in the urgent care unit inside the clinic or referred to the proper management pathway.

## 2.10 Statistical Analysis

The sample size required to reach significant in the three primary outcomes in the study’s multi-intervention approach is 180 participant (90 participants in each group). Sample size was calculated with Giga sample size online calculator [69], according to a pilot analysis of 50 participants matching study protocol, with a power of 80% with alpha level of 5% to detect the minimal difference of each primary outcomes in the study.

For 1^st^ outcome, the baseline medication possession ratio (MPR) for those 50 participants was 0.93 ± 0.09 (mean ± SD), we determined that a target of 82 participants per group would be required for a minimum detectable effect of 0.035 between both groups. A total sample size of 180 was calculated, assuming dropout rate of 10% in both groups.

For 2^nd^ outcome, the mean body mass index (BMI) (mean ± SD) of the 50 participants was 31.2 ± 6.4, and the total number of participants required to detect minimum detectable difference of 2.5 in BMI between groups was 180 participants, powered for 80% with α equal to 0.05, considering drop rate of 10% throughout the study period.

In addition, for 3^rd^ outcome to detect minimal difference of 0.5% in HbA1c between groups with mean HbA1c = 7.7 ± 1.3 (mean ± SD) at baseline (for the same 50 participants), a total sample size of 184 participants were calculated with 84 participants per group were required, considering 10% expected dropout rate during the follow-up period.

For data analysis, the difference between both groups will be tested for normality using the Shapiro–Wilk test. Data will be presented as percentages for categorical variables or mean ± SD or median (25th, 75th percentiles) for continuous variables. Chi-square test will be used for the categorical variables, whereas student’s t-test will be used for normally distributed continuous variables, or Mann–Whitney U test for non-normally distributed continuous variables.

Analyses will be performed using IBM SPSS Statistics (version 26), and differences will be considered significant for a p-value of <0.05.

Data verification will be performed on a weekly basis, and any missing data will be completed within 1 week of initial data collection and will be doubled-checked by two researchers before data analysis. Missing data in the final dataset will be filled by multiple imputation of the incomplete multivariate data using NORM® programme (version 2.03) integrated with SPSS, under a normal model and with two-level hierarchical linear modeling (HLM) analysis.

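### The stated sample sizes reproduce only with a one-sided 5% test that the protocol never declares; with two-sided tests, power at 81 evaluable per group is about 68–70%, not 80%

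*Protocol*

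**What the plan says.** All of the sizing is in Protocol section 2.10 (Statistical Analysis). The headline is that the size needed for the three primary outcomes in the "multi-intervention approach is 180 participant (90 participants in each group"), derived from a 50-patient pilot "with a power of 80% with alpha level of 5% to detect the minimal difference of each primary outcomes in the study".

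The three supporting calculations are:

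- **MPR:** the pilot value "for those 50 participants was 0.93 ± 0.09 (mean ± SD"), and then "we determined that a target of 82 participants per group would be required for a minimum detectable effect of 0.035 between both groups". The total with 10% dropout is given as 180.
- **BMI:** SD 6.4, difference 2.5, total 180, "powered for 80% with α equal to 0.05, considering drop rate of 10% throughout the study period". No per-group figure is given.
- **HbA1c:** SD 1.3, difference 0.5, and "a total sample size of 184 participants were calculated with 84 participants per group were required", again with 10% dropout.

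For the analysis, continuous outcomes are compared between groups by Student's t-test, or by Mann–Whitney if not normally distributed, and "differences will be considered significant for a p-value of <0.05". Neither the sizing nor the analysis text says whether tests are one- or two-sided.

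Section 2.6 (Randomization) generates a list of 239 random numbers. The protocol does not explain how 239 relates to 180.

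**The concern.** The inputs, the sample sizes, the power and the tests are all stated, so they can be checked against one another, and they do not fit. A reader who sees 80% power and 5% alpha beside ordinary t or Mann–Whitney tests at p<0.05 will take the tests as two-sided. On that reading the stated sizes are about a fifth too small.

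What is at stake is how a null result is read. At 68–70% power, almost one true effect in three of the planned size would be missed on each outcome, against the one in five that the protocol claims. A non-significant result would then count as stronger evidence against the intervention than the design can supply.

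The totals also disagree: one of the three primary outcomes is said to need 184, yet the trial is set at 180 for all three.

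**Working it through.** **Inputs (Protocol section 2.10).** Alpha 5%, power 80%, dropout 10%, 90 randomised per group. SD and difference: MPR 0.09 and 0.035; BMI 6.4 and 2.5; HbA1c 1.3 and 0.5. Allocation is 1:1 (Figure 1).

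**Formula.** n per group = 2 (z_alpha + z_beta)² (SD/d)². The factor (z_alpha + z_beta)² is 6.183 for a one-sided 5% test (1.645 + 0.842) and 7.849 for a two-sided one (1.960 + 0.842). The ratio (SD/d)² is 6.612 for MPR, 6.554 for BMI and 6.760 for HbA1c.

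**Step 1: reproduce the plan's figures.**

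| Outcome | One-sided 5% | Two-sided 5% | Stated |
|---|---|---|---|
| MPR | 81.8, so 82 | 103.8, so 104 | 82 per group |
| BMI | 81.0, so 82 | 102.9, so 103 | 180 in total |
| HbA1c | 83.6, so 84 | 106.1, so 107 | 84 per group |

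The one-sided column matches 82 and 84 exactly and is consistent with 180 for BMI. The two-sided column matches none. Rounding of the SDs does not close the gap: two-sided, MPR with SD 0.085 still needs 93 per group, BMI with SD 6.35 needs 102, and HbA1c with SD 1.25 needs 99.

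**Step 2: power of the trial as sized.** 90 × 0.9 = 81 evaluable per group. Power by noncentral t:

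| Outcome | Two-sided, 81 | Two-sided, 90 (no dropout) | One-sided, 81 |
|---|---|---|---|
| MPR | 69.1% | 73.7% | 79.4% |
| BMI | 69.5% | 74.1% | 79.7% |
| HbA1c | 68.2% | 72.8% | 78.6% |

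The normal approximation gives 69.7%, 70.1% and 68.7% two-sided at 81.

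**Step 3: differences detectable with 80% power at 81 per group, two-sided.** The t-test needs a standardised difference of 0.443. Multiplied by the SD:

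- MPR: 0.443 × 0.09 = 0.040
- BMI: 0.443 × 6.4 = 2.8
- HbA1c: 0.443 × 1.3 = 0.58 (0.57 by normal approximation)

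**Step 4: the totals and dropout.**

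- The plan's own needs are 82 (MPR) and 84 (HbA1c) per group, but 81 remain after 10% dropout.
- Multiplying by 1.1: 2 × 82 × 1.1 = 180.4 and 2 × 84 × 1.1 = 184.8, close to the stated 180 and 184.
- Dividing by 0.9: 164/0.9 = 182.2 and 168/0.9 = 186.7.
- For BMI the method cannot be told. The unrounded n gives 2 × 81.04/0.9 = 180.1, and the rounded n gives 2 × 82 × 1.1 = 180.4.

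**Step 5: what each part costs.** One-sided HbA1c power is 79.9% at 84 per group and 78.6% at 81, a loss of about one point. Moving from one-sided to two-sided at 81 per group costs about ten points (78.6% to 68.2%).

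**Step 6: two-sided totals.** For two-sided 80% power, dividing by 0.9 gives totals of about 232 (MPR), 229 (BMI) and 238 (HbA1c).

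**The case against.** The strongest reply is that the protocol never says two-sided. Its expected outcomes in section 1.4 are directional (better adherence, more patients at target), and the stated sizes match a directional calculation. On that reading power is 79–80%, and there is little to correct. What stands is that the 68–70% figure is conditional on two-sided analysis. But directional expectations do not specify a test, section 2.10 describes undirected comparisons, and a one-sided 5% criterion would itself have to be declared. The text needs correcting on either reading.

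A second reply is that section 2.6 generates 239 numbers, close to the two-sided HbA1c total of 238. After 10% dropout, 239 would leave about 107 per group and two-sided power of 80–81%. A reader might infer that a larger trial was really intended. The documents do not support this: section 2.10 states 180, and 239 is unexplained. It does have to be reconciled before any power is restated.

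Other tempting readings also go too far:

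- **That 180 against 184, or the dropout step, causes the shortfall.** Together they cost about one point; sidedness accounts for nearly all of it.
- **That dropout was handled by multiplying by 1.1 throughout.** This fits MPR and HbA1c, but the protocol states no method and BMI fits either.
- **That the chi-square test settles the sidedness.** All three sized outcomes are continuous, so it has no bearing.
- **That baseline adjustment would restore 80% without more patients.** This needs a baseline-to-exit correlation that the protocol does not give. For MPR it also needs a baseline value per participant, whereas section 2.8.1 calculates MPR from consent onward.

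Finally, MPR is capped at 1 with mean 0.93 and may be analysed by Mann–Whitney, so its power figure is a normal-theory approximation. That is fair, but the protocol's own 82 rests on the same approximation.

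**Conclusion.** Wrong as written. The stated sizes correspond to one-sided 5% tests that the protocol does not declare. Under the two-sided tests that its analysis text would ordinarily mean, 180 randomised with 10% dropout gives about 69% (MPR), 70% (BMI) and 68% (HbA1c) power instead of 80%. Even if one-sided tests were declared, power would be 79–80%.

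The conflict between 180 and 184, and the 81 evaluable against 82 and 84 required, are separate and minor for power, but they are plain contradictions that need no assumption about sidedness.

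The result rests on the pilot SDs and planned differences in section 2.10, exactly 10% dropout, equal groups, an unadjusted comparison and normal theory. The figures are per outcome. Power to reach significance on all three together cannot exceed the lowest, 68%. Under independence it would be about 33% (0.691 × 0.695 × 0.682), but the protocol gives no correlations, so that figure is only illustrative.

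**What to change.** In section 2.10:

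1. Declare the primary comparisons two-sided at 5%.
2. Replace the 80% claim with about 68–70% power per outcome at 81 evaluable per group, or give the detectable differences at 80% power: about 0.040 (MPR), 2.8 (BMI) and 0.58 percentage points (HbA1c). Mark these as normal-theory approximations, given the cap on MPR and the possible Mann–Whitney analysis.
3. Give one total, and reconcile 180, 184 and the 239 numbers in section 2.6. If the total is not 180, recompute item 2 for it.
4. State the dropout method and divide by 0.9.

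If the total stays at 180, this changes wording only: no visit, test or treatment is affected. The cost is a less favourable power statement. Keeping two-sided 80% power for the planned differences would instead need about 238 in total, set by HbA1c.

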## 2.8 Study Procedures

Eligible participants will sign the consent form at the physician’s office, and laboratory results will be recorded as baseline data. If the patient’s medical record does not contain recently updated laboratory tests from the previous three months, laboratory tests will be scheduled for blood sample collection in the clinic and tested in Abu Dhabi Health Services Company (SEHA) central laboratory, and the same process will be performed at the conclusion of the follow-up period after 12 months. Laboratory tests in the study protocol included gylcated hemoglobin A1c (HbA1c), estimated Glomerular Filtration Rate (eGFR), complete blood count, electrolyte panel including potassium and magnesium levels, serum creatinine levels, and albumin/creatinine ratio.

Laboratory and clinical assessments in the study protocol included BP measurement and laboratory tests HbA1c level, low-density lipoprotein cholesterol (LDL-C) level, complete blood count, electrolyte panel including K and Mg levels, eGFR, serum creatinine level, and albumin/creatinine ratio. BP measurements and laboratory tests will be performed according to the standard procedures for BP measurement and blood sample withdrawal at the clinic.

In addition, each participant in both groups will undergo individual assessments at initial visit and study exit including medication adherence by clinical pharmacist and diet and exercise assessment by specialized dietician.

During the study period, the control group will receive the usual care provided in the clinic including the routine follow-up and clinical assessments (as needed). The routine usual care will include follow-up schedule every 3 months with the treating physician, vital signs monitoring in the visited clinic, physician consultation, any additional investigational services or laboratory tests requested by the treating physician depending on each patient’s condition, patient counselling at the pharmacy counter, dietitian counselling service if requested by the patient or referred by the treating physician, and a call reminder from the clinic call centre 3 days before the appointment.

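### Section 2.10 fixes an unadjusted test, chosen by a normality pre-test, for every continuous outcome, although HbA1c, BMI and other outcomes have a baseline value in both arms

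*Protocol*

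**What the plan says.** Protocol section 2.10 sets one rule for continuous outcomes. First, "the difference between both groups will be tested for normality using the Shapiro"–Wilk test; then a Student's "t-test will be used for normally distributed continuous variables, or Mann–Whitney U test for non-normally distributed continuous variables". The threshold is that "differences will be considered significant for a p-value of <0.05", with no statement of one or two sides. No covariate, change score or regression model is named for any outcome. The only model mentioned is a two-level hierarchical linear model, in the closing sentence on multiple imputation, with no outcome, levels or covariates given.

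Baseline values are collected in both arms. Section 2.8 records laboratory results as baseline and repeats them after 12 months, and "each participant in both groups will undergo individual assessments at initial visit and study exit" for adherence, diet and exercise. Section 2.8.2 takes anthropometry at enrolment and exit, and food logs for carbohydrate and energy intake before the baseline visit and at exit, for all participants.

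MPR is the exception. Section 2.8.1 calculates it from the date of consent, excludes earlier supply, caps it at 1, and computes it once after 12 months.

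The sample size in section 2.10 rests on differences in means, "with a power of 80% with alpha level of 5% to detect the minimal difference of each primary outcomes in the study". For MPR the pilot gave "0.93 ± 0.09 (mean ± SD") and "a target of 82 participants per group would be required for a minimum detectable effect of 0.035 between both groups".

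**The concern.** There are two linked problems.

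First, the plan leaves baseline information unused. An unadjusted comparison of exit values keeps in the error term all the between-patient variation that the baseline would explain. It also passes on part of any chance imbalance at entry. With a BMI SD of 6.4 and 81 per arm, the standard error of the baseline difference is 6.4 × √(2/81) ≈ 1.0, against a target effect of 2.5. Under a normal approximation, about one randomisation in three (32%) would differ by more than 1 BMI unit at entry. If changes are meant instead, the result is different again, and section 2.10 leaves that choice open.

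Second, the normality gate decides after the data are seen whether the trial reports a difference in means, for which it was sized, or a rank comparison, for which it was not. The gate is also loosely defined. Two independent groups have no per-patient difference to test for normality, so it is unclear what the Shapiro–Wilk test would be applied to.

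**Working it through.** **Inputs (Protocol section 2.10).** Alpha 5%, power 80%. MPR: SD 0.09, difference 0.035, 82 per group. BMI: SD 6.4, difference 2.5, total 180. HbA1c: SD 1.3, difference 0.5, 84 per group. The planned size "is 180 participant (90 participants in each group"); less 10% dropout this leaves 90 × 0.9 = 81 per arm.

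**Step 1: reproduce the plan's figures.** For an unadjusted comparison of two means, n per arm = 2(z_α + z_β)² × SD²/difference², with z_β = 0.8416.

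| Outcome | One-sided 5% (z_α = 1.645) | Two-sided 5% (z_α = 1.960) | Stated |
|---|---|---|---|
| MPR | 81.8 → 82 | 103.8 → 104 | 82 |
| BMI | 81.0 → 82 | 102.9 → 103 | per-group figure not given |
| HbA1c | 83.6 → 84 | 106.1 → 107 | 84 |

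The stated numbers match an unadjusted, one-sided calculation.

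**Step 2: unadjusted power at 81 per arm (noncentral t).**

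| Outcome | Difference/SD | Two-sided 5% | One-sided 5% |
|---|---|---|---|
| MPR | 0.389 | 69.1% | 79.4% |
| BMI | 0.391 | 69.5% | 79.7% |
| HbA1c | 0.385 | 68.2% | 78.6% |

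The plan's 80% is essentially met if testing is one-sided. The fall to 68–70% comes from testing two-sided.

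**Step 3: what adjustment would add.** With correlation r between baseline and 12-month values, ANCOVA uses SD × √(1 − r²), and a change-score t-test uses SD × √(2(1 − r)). No r is given in the documents, so a range is assumed. Power is two-sided 5%, 81 per arm:

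| Assumed r | 1 − r² | 2(1 − r) | HbA1c ANCOVA | HbA1c change | BMI ANCOVA | BMI change |
|---|---|---|---|---|---|---|
| 0.3 | 0.91 | 1.40 | 72% | 54% | 74% | 55% |
| 0.5 | 0.75 | 1.00 | 80% | 68% | 81% | 70% |
| 0.7 | 0.51 | 0.60 | 93% | 88% | 93% | 89% |

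Reaching 80% needs r of roughly 0.5 for either outcome. Below r = 0.5 a change score is worse than ignoring baseline; at 0.5 it is equal.

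**Step 4: the normality gate and MPR.** The cap lies (1 − 0.93)/0.09 = 0.78 SD above the pilot mean, so a normal shape is implausible. As a check, 81 values were drawn 3,000 times from each of two assumed shapes with that mean and SD: a beta distribution, and a normal distribution censored at 1. Shapiro–Wilk rejected normality in essentially every run. Under these shapes, MPR would be sent to Mann–Whitney although it was sized on a mean difference of 0.035.

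**The case against.** The strongest reply is that in a 1:1 randomised comparison the unadjusted t-test is valid and unbiased, and its confidence interval already allows for chance imbalance. Adjustment is then a matter of efficiency, and covariates are commonly left to a statistical analysis plan, which is not at hand. The first part stands: this is lost precision, not bias. The second stands only in part, because section 2.10 is not silent. It names the test for every continuous outcome. Nor does Mann–Whitney cost much power: on normal data about 1 to 2 points at 81 per arm. The objection to the gate is that the reported quantity changes.

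Several stronger readings are tempting, and the protocol does not support them:

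- A reader might infer that omitting baseline causes the 68–70% power. It does not. The sample size already assumed an unadjusted comparison, and the shortfall appears only if a calculation that fits one-sided 5% is followed by a two-sided test. That is a separate sample-size issue.
- A reader might infer that exit values are certainly compared. Section 2.10 says neither exit values nor changes. For an outcome as highly correlated as r = 0.9, a change score would do nearly as well as ANCOVA (variance factors 0.20 and 0.19), so a very large BMI gain cannot be claimed against every reading.
- A reader might infer that every outcome has a baseline. MPR, the first outcome used for sizing, has none within the trial.
- A reader might expect the pilot to supply r. No repeat measurements on the 50 pilot participants are documented.
- A reader might take the hierarchical model for an adjusted analysis. It is attached to the imputation sentence and undefined, so it does not displace the stated tests.

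**Conclusion.** The point holds in this form. Section 2.10 fixes an unadjusted test chosen by a normality pre-test and leaves exit value or change undecided, while baselines for HbA1c, BMI and other outcomes are collected in both arms. The gate can swap the mean difference used for sizing for a rank comparison, and for MPR that is likely.

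The gain from ANCOVA over an unadjusted comparison of exit values, at 81 per arm and two-sided 5%, runs from about 4 points of power at r = 0.3 to about 24 at r = 0.7 for HbA1c and BMI. It rests on assumed correlations, on the pilot SDs applying at 12 months, on 10% dropout, and on two-sided testing, which the protocol does not state. At low r, adjustment alone would not restore 80%. This is a worthwhile improvement in precision and clarity; it does not show that the planned test is invalid.

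**What to change.** In section 2.10, replace the test rule for continuous outcomes:

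- For each continuous 12-month outcome with a baseline value, use ANCOVA: linear regression on group and the baseline value. Report the adjusted mean difference with its 95% CI, with robust or bootstrap standard errors if residuals are skewed.
- Drop the Shapiro–Wilk gate and keep Mann–Whitney as a sensitivity analysis.
- For MPR, which has no trial baseline, report the difference in means with a robust or bootstrap 95% CI. Do not require a pre-study covariate, since extracting pre-consent refills would be an extra data step and might be incomplete.
- State whether tests are one- or two-sided, and say what the hierarchical model in the missing-data sentence is for, so that it does not read as a second, undefined analysis.

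The cost is a change of wording before analysis. The ANCOVA uses only values already scheduled for collection, so no new data or visits are needed.

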In each food log section, the participants can describe the consumed food or beverage, and any other oil, fats, sauces, or condiments used in preparation or added during food serving, in addition to the time and occasion of each meal or snack. During the session, the research dietitian will review the food logs, clarify any unclear entries or descriptions, and estimates the average daily energy intake and dietary carbohydrate value for each participant.

D) Exercise and Physical Activity Reinforcement Counseling

For each participant in the intervention group, the dietitian will develop individual exercise targets based on their clinical condition and motivation level while taking into consideration each participant’s current eating patterns and willingness to adhere to exercise and lifestyle modifications.

Any identified challenges that limit the patient from being physically active will be discussed with the patient, and an action plan will be discussed with the treating physician and documented in the patient’s file.

Anthropometric measurements will be obtained by registered nurses in the clinic at the time of enrolment, before exiting the study for all participants, and at each follow-up visit for the intervention group. Body weight and height will be measured without shoes using a standard monthly calibrated scale at the Dietitian Office (Tanita Corporation, Japan). The same nurse will measure the patients’ waist circumference just marginally above the hipbone and their hip circumference at the largest part of their buttocks.

In addition, to explore the type of most recurring physical activity in our intervention population, we added additional table to the questionnaire to describe the type of physical activity, intensity of the purposive activity, average number of days per week for each activity, and duration of each activity (Appendix 14).

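### Section 2.10 names only unadjusted two-sample tests for continuous outcomes and does not say whether exit value or change is compared, although entry and exit values are planned in both arms for BMI, HbA1c and most other outcomes

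*Protocol*

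**What the plan says.** **The tests.** Protocol section 2.10 names chi-square for categorical variables. For continuous variables a "t-test will be used for normally distributed continuous variables" and the Mann–Whitney U test otherwise. No covariate enters any between-group comparison. Hierarchical linear modelling appears only in the closing sentence on imputation of missing data. The section does not state whether the exit value or the change from entry is tested.

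**The baselines.** Section 2.8 says that "each participant in both groups will undergo individual assessments at initial visit and study exit", and it plans laboratory tests and blood pressure at entry and after 12 months, with HbA1c and LDL-C among the listed assessments. Section 2.8.2 says: "Anthropometric measurements will be obtained by registered nurses in the clinic at the time of enrolment, before exiting the study for all participants". The same section plans three-day food logs for everyone before the first visit and at exit, giving carbohydrate and energy intake at both times.

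**The exception.** Section 2.8.1 counts MPR from the date of consent and calculates it once, after 12 months. The baseline MPR quoted in section 2.10 belongs to the 50 pilot participants.

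**The sizing.** Section 2.10 sizes the trial "with a power of 80% with alpha level of 5% to detect the minimal difference" of each primary outcome, using raw pilot SDs. For BMI the "total number of participants required to detect minimum detectable difference of 2.5 in BMI between groups was 180 participants", with an SD of 6.4. For HbA1c the difference is 0.5 with an SD of 1.3.

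**The concern.** BMI and HbA1c vary widely between patients at entry, and the intervention cannot alter that spread. If exit values are compared with no adjustment, all of it stays in the error term. Baseline adjustment removes the part that entry values predict, which could be large for BMI over 12 months. Section 2.6 describes a simple random sequence with no stratification on baseline values, so the design does not remove this variation either.

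Two things are at stake. A useful effect on BMI, HbA1c or diet intake could be missed although the collected data could show it. And because the compared quantity is left open, the choice between exit value and change could be made after the data are seen.

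**Working it through.** **Inputs.** From section 2.10: BMI difference 2.5, SD 6.4; HbA1c difference 0.5, SD 1.3; MPR difference 0.035, SD 0.09; 90 per arm; 10% dropout, so 90 × 0.9 = 81 analysed per arm. Assumed: two-sided testing (the rule is only that "differences will be considered significant for a p-value of <0.05"); exit SD equal to the pilot SD; and the baseline-to-exit correlation r, which the protocol does not give and which is therefore shown over a range.

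**1. The plan's own figures.** n per arm = 2(z_α + z_β)²(SD/difference)², with z_β = 0.842.

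- One-sided 5% (z_α = 1.645): MPR 12.365 × 6.612 = 81.8, so 82; BMI 12.365 × 6.554 = 81.04, so 82; HbA1c 12.365 × 6.76 = 83.6, so 84. The stated 82 (MPR) and 84 (HbA1c) are reproduced. For BMI, 2 × 82 × 1.1 = 180.4 agrees with the stated total of 180.
- Two-sided 5% (z_α = 1.96): 104, 103 and 107. These do not match.

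**2. Unadjusted comparison of exit values, 81 per arm, two-sided 5%.** SE = SD × √(2/81) = SD × 0.1571.

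- BMI: SE = 1.006; power = Φ(2.5/1.006 − 1.96) = Φ(0.526) = 0.70.
- HbA1c: SE = 0.2043; power = Φ(0.5/0.2043 − 1.96) = Φ(0.488) = 0.69.
- BMI difference detectable with 80% power: 2.80 × 1.006 = 2.82.

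**3. With baseline in the model.** The SD is multiplied by √(1 − r²). For a change score it is multiplied by √(2(1 − r)).

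| r | √(1 − r²) | Power, BMI 2.5 | Power, HbA1c 0.5 | Detectable BMI, adjusted | Detectable BMI, change score |
|---|---|---|---|---|---|
| 0.3 | 0.954 | 0.74 | 0.73 | 2.69 | 3.33 |
| 0.5 | 0.866 | 0.82 | 0.81 | 2.44 | 2.82 |
| 0.6 | 0.800 | 0.87 | 0.86 | 2.25 | 2.52 |
| 0.7 | 0.714 | 0.94 | 0.93 | 2.01 | 2.18 |
| 0.8 | 0.600 | 0.99 | 0.98 | 1.69 | 1.78 |
| 0.9 | 0.436 | >0.99 | >0.99 | 1.23 | 1.26 |

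**4. Thresholds.** Adjusted power reaches 80% at r of about 0.46 for BMI and 0.49 for HbA1c. The detectable BMI difference is halved when √(1 − r²) = 0.5, that is at r = 0.866.

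**5. If all 90 per arm are analysed.** Unadjusted power is 0.75 (BMI) and 0.73 (HbA1c), and 80% is reached at r of about 0.35 and 0.39.

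**The case against.** **An unadjusted test between randomised arms is valid.** This stands. It controls the type I error, and its standard error already allows for chance imbalance at entry. The point is about efficiency, not bias.

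**Covariates are often left to the SAP, which is not shown.** This would settle the matter if section 2.10 were silent. It is not: it names the tests, and an SAP that used another primary comparison would depart from it.

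**A change score may have been meant, and it already uses the baseline.** Section 2.10 allows this reading. A reader might infer from the cross-sectional SDs in the sizing, or from the phrase about study exit in section 1.3, that exit values are compared. But that phrase belongs to the third secondary outcome, and the tested quantity is nowhere defined. If change was meant, the further gain for BMI at high r is small (1.26 against 1.23 at r = 0.9). At r = 0.5 a change score gains nothing over the exit value, and below that it loses precision, whereas the adjusted model is never less precise apart from its one degree of freedom.

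**Stronger readings that the protocol does not support.**

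- *MPR could be adjusted too.* The pilot baseline invites this, but no baseline MPR is planned for trial participants. A prior-year MPR would need its own definition and extraction.
- *Adjustment more than halves the detectable BMI difference.* This needs r above about 0.87, which nothing in the protocol establishes.
- *Adjustment restores the stated 80% power.* The shortfall comes from sizing that matches only a one-sided 5% test. If the test were one-sided, unadjusted power at 81 per arm would already be about 0.80 for BMI and 0.79 for HbA1c.

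**Conclusion.** The point holds for continuous outcomes with a planned baseline: BMI and other anthropometry, HbA1c, blood pressure, LDL-C and other laboratory values, and carbohydrate and energy intake. For these, section 2.10 names a less precise comparison than the data allow and leaves the compared quantity undefined. It does not hold for MPR.

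Against an unadjusted comparison of exit values, the gain at moderate correlation (r = 0.5 to 0.6) is about 12 to 17 percentage points of power for BMI and HbA1c. It is only about 4 points at r = 0.3. These figures rest on 81 analysed per arm, two-sided testing, equal SDs at entry and exit, and assumed values of r. The change is worth making but does not correct an invalid analysis. The one-sided sizing needs its own correction.

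**What to change.** In section 2.10, for each continuous outcome with a planned entry value in both arms:

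- make the primary comparison a linear model of the 12-month value on arm and the same variable at baseline;
- report the adjusted mean difference with its 95% confidence interval;
- keep the t-test or Mann–Whitney U test as a sensitivity analysis, stating whether it is applied to the exit value or to the change;
- state the value or range of r assumed in any power statement that relies on adjustment.

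Leave MPR as an unadjusted comparison and say so. State the sidedness of the tests and correct the sample size separately, without citing baseline adjustment as the remedy.

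The cost is a change of wording and about one degree of freedom per model. No new visit, measurement or data extraction is needed.
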